**STUDY PROCEDURES**

1. ***Procedures***

After obtaining written consent and written clearance from the primary care physician or oncologist is provided, a baseline measurement appointment will be scheduled. Measurements will include those described in detail below. All measurements described below will occur prior to randomization and at six-months. For all measurement visits, participants will be provided free parking or bus/subway tokens.

**Blood assays as outcomes.** Participants will undergo a fasting blood draw at baseline and six-months later at the same time of day through Penn’s CTSA-funded shared resource clinics. A total of 50.0 mL will be drawn per participant at baseline and again at six-months. All aliquots will be stored until the end of the study for analysis. Assays will be completed through the Human Immunology Core ((HIC) a shared resource of the Perelman School of Medicine, under the direction of [name])). CTCs will be completed in the laboratory of [name] at the University of Michigan (Co-I).

- sICAM-1 will be analyzed using an R&D systems enzyme linked immunoabsorbent assay.[99,104] The inter-assay coefficient of variation and sensitivity are 5.4%, and 0.049-0.254 ng/mL, respectively.[118]
- sVCAM-1 will be analyzed using an R&D systems enzyme linked immunoabsorbent assay. The inter-assay coefficient of variation and sensitivity are 7.7%, and 0.17-1.26ng/mL, respectively.[119] Both assays will be repeated in duplicate for quality control.

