**Body weight, height, waist circumference, and sagittal abdominal diameter** will be assessed using a digital scale, scale mounted stadiometer, Gulick tape measure, and abdominal caliper. Height will be assessed at baseline only.

**Diet.** In order to ensure that any effects noted are due to exercise rather than dietary changes, participants will complete a 3-day food record at baseline and follow-up.[135] These food records will be entered and analyzed using Nutrition Coordinating Center software by Penn CTRC registered dietitians trained in its use.

**Accelerometry**. Participants will be asked to wear a 2009 Actigraph GT3X 16 MB and Tractivity triaxial accelerometers for one week before and after the study to objectively assess their activity level.[136] Our research team has experience with objective PA assessment, and the appropriate software needed for analysis of these data.[137-139]

**Self-Reported Questionnaires.** Participants will complete questionnaires relating to demographics,[91,92] alcohol and smoking habits,[140] current medicine and supplement usage.[141] Overall quality of life will be assed using The Functional Assessment of Cancer Therapy-Colorectal (FACT-C),[142] and the SF-36.[143] In addition, participants will complete a series of strategically selected valid and reliable questionnaires to assess issues known to influence the quality of life of people with CC, as acknowledged by the Institute of Medicine and others.[144,145] Pain will be assessed using the Brief Pain Index.[146] Sleep will be assessed using the Pittsburgh Sleep Quality Index.[147] Bowel function will be assessed using the Assessment of Bowel Function Questionnaire.[148] Fatigue will be assessed using the Brief Fatigue Inventory.[149] Neuropathy will be assessed using the Neuropathic Pain Scale.[150] Lastly, participant’s will complete a healthcare utilization and musculoskeletal injury questionnaire at 6-months asking about any healthcare encounters and injuries experienced while in the study that were not identified in the weekly in-person or phone follow-ups, as used in our prior exercise intervention studies among cancer survivors.[93,151]

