**Medical record abstraction.** Medical characteristics such as tumor pathology, surgical history, chemotherapy treatment plan, laboratory tests, and any prior comorbid conditions will be extracted from pathology reports and/or the electronic medical record implemented in all practices at the University of Pennsylvania. This data will be collected for all potentially eligible study participants.

**Randomization.** After completion of the eligibility screening and baseline measurements, participants will be randomized evenly to one of three study arms. Randomization will be stratified by stage of cancer (stage II vs. III). Participants will be randomized by the study coordinator using electronic randomization

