***2. Statistical Analysis***

**Primary Outcomes**

We will randomize 13 participants to each of the three study arms (control, 150 min∙wk^-1^, 300 min∙wk^-1^), to achieve 10 per group who complete the study (76% completion rate). Participants who have a cancer recurrence during the study will be excluded from the primary outcome analysis. The sample size is powered for the primary outcome biomarkers (sICAM-1 and sVICAM-1) with a hypothesis for a linear trend. The standard deviation of sICAM-1 and sVCAM-1 are 30 and 103 units, respectively. Against the hypothesis of a dose-response relationship with decreases of 22 and 44 units for low- and high-dose respectively for sICAM-1 and 74 and 148 units for sVCAM-1, 30 subjects provide 80% power for two, two-sided 0.025 tests (one for sICAM-1 and one for sVCAM-1, with the Type I error adjusted to maintain the experiment-wise error rate of 0.05). These reductions are consistent with prior exercise interventions in non-cancer survivorship populations, where clinically significant reductions in sICAM-1 and sVCAM-1 occur with 30 and 75 unit changes, respectively.[99-103]

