The feasibility of exercise will be quantified by comparing the proportion of participants in each group who achieve ≥80% of their prescribed exercise dose. The incidence of exercise dose-alteration will be quantified by comparing the proportion of participants who require a dose-reduction or cessation of exercise in each group. The indication for the dose-reduction or cessation will also be described qualitatively. As this aim intends to describe feasibility, we state no directional hypothesis. For the primary biomarker outcomes, we will use a linear mixed-effects regression to compare the change in biomarker levels for each group while controlling for other variables likely to influence sICAM-1 and sVCAM-1 (in addition to the effects from treatment group). Potential confounders (e.g., change in diet, sleep, or body weight) will be screened using univariate models; those that appear to be associated with the outcome will be entered sequentially in multivariate models. We will initially fit models including dose as a linear term, and assess model fit using standard methods. Alternatives to a linear dose trend include transformations of dose such as average actual dose, log-transformed dose per week, or second-order polynomial (i.e., dose and dose^2^). In the event that a dose-response relationship does not exist, we will compare each of the two intervention groups (low- and high-dose exercise) to the control arm separately. Using a two-sided t-test we will have 80% power to detect a difference in of 32 units for sICAM-1 and 112 units for sVCAM-1, utilizing the sequential testing procedure of Benjamini and Hochberg to protect the family-wise error rate.[155]

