**Secondary Outcomes**

The sample size of the COURAGE trial is sufficient to explore the dose-response effects of exercise on VAT and fasting insulin. In the STRRIDE study, changes in VAT among the control, low-dose exercise, and high-dose exercise groups were +8.6%, +1.7%, and –6.9%, respectively.[106-108] Using these point-estimates and a standard deviation of ±17%, we will have 80% power to test the hypothesis of a linear dose-response relationship between exercise and VAT across the three study groups with a type-I error rate of 0.05. In the STRRIDE study, changes in fasting insulin among the control, low-dose exercise, and high-dose exercise groups were +1.1 *μ*U/mL, –0.5 *μ*U/mL, and –0.9 *μ*U/mL, respectively.[114] Using these point-estimates and a standard deviation of ±0.7 *μ*U/mL, we will have ≥80% power to test the hypothesis of a linear dose-response relationship between exercise and fasting insulin across the three study groups with a type-I error rate of 0.05. For our exploratory correlational analysis (i.e., exploratory aim), we will have 80% power to detect a correlation of *≥*0.40 between the exercise-induced improvements in VAT and the exercise-induced improvements in fasting insulin.

For the outcomes of VAT and fasting insulin, we will use a linear mixed-effects regression model to compare the change in outcome levels for each treatment group while simultaneously controlling for other variables identified to influence VAT and fasting insulin (i.e., a multivariable adjusted linear mixed model). Potential confounders (e.g., changes in diet, sleep, and smoking) will be screened using univariate models; those that appear to be associated with the outcome will be entered sequentially in multivariate models. We will fit models including dose as a linear term, and assess model fit using standard methods. Alternatives to a linear dose trend include transformations of dose such as average actual dose, log-transformed dose per week, or second-order polynomial (i.e., dose and dose^2^). In the event that a dose-response relationship does not exist, we will compare each of the two intervention groups (low- and high-dose exercise) to the control arm separately. In our exploratory correlational analyses, we will calculate Pearson’s product-moment correlation coefficient (*r*) to quantify the strength of the relationship between the exercise-induced improvements in VAT and the exercise-induced improvements in fasting insulin.

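### The dose models may adjust for changes measured after randomisation, picked by their association with the outcome, and no model free of them is named as primary

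*Protocol*

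**What the plan says.** All of this is in the protocol, section Study Procedures, unless stated otherwise.

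- **Primary biomarkers** (Statistical Analysis, Primary Outcomes). A linear mixed-effects regression will "compare the change in biomarker levels for each group while controlling for other variables likely to influence sICAM-1 and sVCAM-1". On the choice of those variables: "Potential confounders (e.g., change in diet, sleep, or body weight) will be screened using univariate models". On what follows: "those that appear to be associated with the outcome will be entered sequentially in multivariate models". No threshold or order of entry is given.
- **Visceral fat and fasting insulin** (Statistical Analysis, Secondary Outcomes). The same procedure with a slightly different list: "Potential confounders (e.g., changes in diet, sleep, and smoking) will be screened using univariate models".
- **Timing** (Procedures). "All measurements described below will occur prior to randomization and at six-months". A change score in diet, sleep, weight or smoking therefore contains a value taken after six months of assigned exercise or waiting.
- **Allocation** (Randomization). After baseline measurement, "participants will be randomized evenly to one of three study arms".
- **Reason given.** Only diet has one (Procedures, Diet): the food records are kept "In order to ensure that any effects noted are due to exercise rather than dietary changes".

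Neither statistical section names an unadjusted model, or one adjusted only for baseline variables, as the primary analysis.

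**The concern.** A confounder of assigned dose would have to influence the assignment. Assignment is random and is made before any of these changes occur, so none of them can confound it. Some may be consequences of exercise.

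The protocol's own background makes this plausible for body weight. It says that exercise reduces visceral fat, that visceral fat secretes cytokines, and that proinflammatory cytokines stimulate sICAM-1 and sVCAM-1. A weight change may lie on that path, and screening on association with the outcome tends to let such a variable in.

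Two things are at stake:

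- **The estimate.** Adjusting for a variable on the causal path takes that part of the effect out of the dose coefficient. The primary hypothesis concerns the effect of assigned dose, and the Overall Objectives say the trial will supply effect sizes for a phase III trial.
- **The error rate.** If a covariate is moved by exercise and also shares unmeasured causes with the biomarker, conditioning on it can make dose and biomarker appear related when they are not.

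**Working it through.** **1. Inputs from the protocol (Primary Outcomes).** "We will randomize 13 participants to each of the three study arms", with 10 per arm expected to complete. SD 30 for sICAM-1 and 103 for sVCAM-1. Decreases of 22 and 44 units (sICAM-1) and 74 and 148 units (sVCAM-1) at low and high dose. Two-sided alpha 0.025 per marker, 80% power.

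**2. The stated power, with no covariates.** Score dose 0, 1, 2. Then SE(slope) = SD/√(2n) = SD/√20, with 28 df.

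- sICAM-1: 30/4.472 = 6.708; 22/6.708 = 3.28; noncentral t power 81.3%.
- sVCAM-1: 103/4.472 = 23.03; 74/23.03 = 3.21; power 79.6%.

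The 80% reproduces, but for a model that contains none of the screened covariates.

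**3. Adding one post-randomisation covariate.** Assumptions that are not in the documents: high dose moves the covariate by *d* of its own SDs (*d*/2 per step), a share *m* of the 44 units runs through it, and an unmeasured shared cause adds a correlation *r* between covariate and biomarker. The within-arm slope of biomarker on covariate is λ = 44*m*/*d* + 30*r*, with the first term zero when there is no true effect. When the covariate is in the model:

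- adjusted effect at high dose = (total effect) − λ*d*. With *r* = 0 this is 44(1 − *m*); with no true effect it is −30*r·d*;
- residual SD = √(900 − λ²);
- variance inflation = 1 + (*d*/2)² × 2/3, because dose scores 0, 1, 2 have variance 2/3.

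*m* = 30%, *d* = 1: λ = 13.2; residual SD √(900 − 174.24) = 26.94; inflation 1.167; SE = 26.94 × √1.167/4.472 = 6.51. The slope is 15.4 per step (31 at high dose). 15.4/6.51 = 2.37, so power is about 50% on 27 df.

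*m* = 50%, *d* = 1: λ = 22; residual SD √(900 − 484) = 20.40; SE 4.93. The slope is 11 (22 at high dose). 11/4.93 = 2.23, so power is about 45%.

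**4. Simulation with the screening step** (covariate kept if univariate p<0.10, an assumed threshold). True effect 44 units, *r* = 0:

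| Mediated | Shift at high dose | Mean estimate | Power |
|---|---|---|---|
| none adjusted for | – | 44 | 81% |
| 10% | 0.5 SD | about 40 | 73% |
| 20% | 0.5 SD | about 35 | 76% |
| 30% | 1 SD | about 31 | 49–50% |
| 50% | 1 SD | about 22 | 44–46% |

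No true effect, nominal 2.5%:

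| *r* | Shift at high dose | Type I error |
|---|---|---|
| 0.5 | none | about 2.4% |
| 0.3 | 0.5 SD | 3.0% |
| 0.5 | 0.25 SD | 3.3% |
| 0.3 | 1 SD | 3.7% |
| 0.5 | 0.5 SD | about 5% |
| 0.5 | 1 SD | about 12% |
| 0.5 | 2 SD | about 25% |

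With positive *r* and a covariate that exercise lowers, the spurious effect is unfavourable. At *r* = 0.5 and a 1 SD shift, always adjusting gives 30 × 0.5 × 1 = 15 units of apparent increase; with screening it is about 14.

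**5. Sensitivity.** With the threshold at p<0.05, 50% mediation gives a slope of about 11 per step and power of 43% for a 1 SD shift or 19% for a 2 SD shift at high dose. In the other direction, a covariate that predicts the biomarker (*r* = 0.5) but is not moved by exercise raises power from 81% to about 89%.

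**The case against.** The best defence has four parts.

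**The lists are examples, and harm is conditional.** A covariate must pass the screen and also be moved by exercise. If exercise does not move it, type I error stays near 2.5% and power can rise. This stands. A reader might infer that the planned analysis necessarily removes part of the effect, or that the 0.025 level is already lost. The documents support neither, since they give no mediated share, shift, correlation or threshold.

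**Controlling for diet has a stated purpose.** Separating exercise from a dietary co-intervention is a recognisable aim. It is, however, a question about a direct effect, and adjusting for a post-randomisation change does not answer it validly when unmeasured causes are shared. It is a reason for a labelled secondary analysis, not for the primary dose test.

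**Baseline may already be in the model.** A reader might add that the plan wrongly leaves out the baseline biomarker value. That is not established. A mixed model with measurements at baseline and six months can carry baseline as a response, and that detail commonly sits in a statistical analysis plan, which was not available here.

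**It is a 39-person feasibility study.** True, and unadjusted group changes can still be computed from the data. But the protocol names these biomarkers as primary outcomes, powers tests on them with multiplicity control, and intends the estimates for a phase III design. The protocol itself states the screening procedure, so a sound analysis plan would have to depart from it.

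**Conclusion.** The point holds in conditional form and should be corrected. For both sets of outcomes the protocol treats changes measured after randomisation as confounders of a randomised dose, selects them by association with the outcome, and names no primary model without them. Diet and sleep are listed for both sets, body weight only for sICAM-1 and sVCAM-1, and smoking only for visceral fat and insulin.

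The mechanism is certain; its size is not given by the documents. With 10 to 50% of the effect mediated and a covariate shift of 0.5 to 1 SD, the 44-unit sICAM-1 effect would be estimated at about 40 to 22 units, with power about 76% to 45% instead of 81%. Under no true effect, type I error would lie between about 2.4% and 12% for shifts up to 1 SD, and about 25% for 2 SD with *r* = 0.5. The high figures need both a large shift and a substantial shared cause. These calculations are for sICAM-1 only; for visceral fat and insulin the argument is the same but no size was computed.

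**What to change.** In both the Primary Outcomes and Secondary Outcomes sections:

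1. Name one prespecified model for each dose test: the outcome on assigned dose, adjusted only for pre-randomisation variables. These are the outcome's baseline value (as a covariate, or as a baseline response constrained equal across arms in the mixed model) and stage, the stratification factor.
2. Delete univariate, outcome-based screening and sequential entry from these tests.
3. Move models containing change in weight, diet, sleep or smoking to a mediation or sensitivity analysis labelled exploratory. The question about diet can be addressed there.

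The cost is a change of wording. No new data are needed, because the baseline values are already collected, and the 80% power statement would then refer to a model without post-randomisation covariates, as its calculation assumes.

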| **Group** | Wk 1 | Wk 2 | Wk 3 | Wk 4 | Wk 5 | Wk 6 | Wk 7 | Wk 8 | Wk 9 | Wk10-26 |
| **Low-Dose (150 min∙wk^-1^)** | 30-60 | 60-90 | 90-120 | 120-150 | 150 | 150 | 150 | 150 | 150 | 150 |
| **High-Dose (300 min∙wk^-1^)** | 30-60 | 60-90 | 90-120 | 120-150 | 150-180 | 180-210 | 210-240 | 240-270 | 270-300 | 300 |
| **Control** | Maintain usual activity level → → → → → → → | | | | | | | | | |

**Monitoring of Exercise Compliance.** Each participant will be provided a Polar heart rate monitor (RS400) for the duration of the study. The RS400 heart rate monitor is able to record 99 exercise sessions of data. Each week the exercise physiologist will download the heart rate data onto a secure study laptop to objectively monitor exercise compliance in terms of frequency, duration, and intensity. The exercise compliance information gathered from the heart rate monitors will be reviewed with the participant for positive reinforcement and to develop and tailor the desired dose of exercise for the following week. This data will be used for the overall exercise compliance monitoring.

**Monitoring of Exercise Participation.** If a participant misses a scheduled exercise session, the exercise physiologist will call the participant. All missed exercise sessions will be documented in standardized study participation logs. Participants who demonstrate poor adherence to the study protocol in terms of participation or compliance will be reminded of the study objectives, and discuss any barriers or obstacles to completing the prescribed exercise dose. Each week, participants will be provided with simple, meaningful, attainable, relevant, and timely (SMART) goals to promote exercise self-efficacy, participation, and compliance.[154]

**Control Group.** The control group of this study is a wait-list delayed intervention. Participants randomized into the control group will be asked to maintain their usual levels of PA until the 6 month visit. Participants will be contacted by telephone once per week by the study coordinator to identify and record any incident health events, and to maintain enthusiasm about participation in the study (despite being in wait-list). After completing study measurements at 6-months, control group participants will be provided with a treadmill delivered and set up in their home (to keep), and a 1-month exercise program tailored to their fitness level.

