***6. Risk/Benefit Assessment***

Once participants are randomized, a certified clinical exercise physiologist will review their current exercise habits and baseline fitness levels and develop a plan to gradually increase the minutes of exercise each week to the prescribed dose. The intensity of their aerobic exercise will be objectively monitored and recorded using heart rate monitors. The certified clinical exercise physiologist will review the objective recording produced by the heart rate monitor each week, and ask the participant if they are experiencing any symptoms that would preclude an increase or maintenance of the currently prescribed dose of exercise. The participants medical care team will be informed of symptom changes and consulted regarding whether is it appropriate to dose-reduce the exercise or cease exercise training all together. In our prior exercise study, the [name] research laboratory suggests 20% of participants will require exercise dose modifications during the 6 month intervention. Participants who are found to have recurrent cancer will be allowed to continue participation in the study, unless their medical oncologist or other physician asks them to stop or reduce their level of exercise. Participants who are found to have a recurrence will be excluded in data analysis. Study staff will work closely with the medical team to ensure the participant receives appropriate medical and psychosocial care and follow-up as necessary.

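### The primary and secondary analyses allow average actual dose, a post-randomisation quantity, to stand in for the assigned dose in the dose-response model

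*Protocol*

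**What the plan says.** Statistical Analysis, Primary Outcomes, powers the trial for a linear trend across three equal randomised arms: "30 subjects provide 80% power for two, two-sided 0.025 tests". The model for sICAM-1 and sVCAM-1 enters dose as a linear term, and its fit is then assessed by unspecified standard methods. Next comes "Alternatives to a linear dose trend include transformations of dose such as average actual dose", followed by log-transformed dose and a quadratic in dose. Each exercise arm is compared with control separately only if no dose-response is found. Secondary Outcomes repeats the sentence on alternatives and the fallback for visceral adipose tissue and fasting insulin.

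Achieved dose depends on health. The Intervention Protocol has a physician decide whether exercise continues, is reduced or stops. Risk/Benefit Assessment says the medical team is "consulted regarding whether is it appropriate to dose-reduce the exercise or cease exercise training all together", and expects 20% of participants to need a dose modification. For the control arm: "Participants randomized into the control group will be asked to maintain their usual levels of PA until the 6 month visit".

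Participants with a cancer recurrence are excluded from the analysis.

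**The concern.** Log dose and dose squared are functions of the assigned dose, so a model using them still compares groups formed by randomisation. Average actual dose is not such a function. The Protocol itself treats it as an outcome: adherence, the share of the prescribed dose completed, is a listed secondary outcome. Placing it in the same list as the other two forms lets the exposure change from something randomised to something that reflects who stayed well enough to exercise.

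The Protocol gives a reason to expect bias in the primary biomarkers. Its Background says proinflammatory cytokines stimulate expression of both sICAM-1 and sVCAM-1. A participant assigned 300 min/wk who falls ill and stops would be analysed at a low dose with a raised biomarker, and that pulls the slope in the hypothesised direction. Because the arm-versus-control comparison is reached only when no dose-response is found, a slope on achieved dose could pre-empt it.

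The variable is also undefined for controls. They have no prescribed dose, and eligibility allows up to 120 min/wk of activity at entry (below 150 in Phase 2). The Protocol does not say whether a control's actual dose is zero or usual activity.

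**Working it through.** **1. The plan's own power figure, on assigned dose.** Inputs from Primary Outcomes: "The standard deviation of sICAM-1 and sVCAM-1 are 30 and 103 units, respectively"; "decreases of 22 and 44 units for low- and high-dose respectively for sICAM-1 and 74 and 148 units for sVCAM-1"; 10 completers per arm; two-sided 0.025. With equal arms and equally spaced doses, the linear contrast is high dose minus control, with SE = SD × √(2/10).

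- sICAM-1: SE = 30 × 0.4472 = 13.42; 44 / 13.42 = 3.28; noncentral t on 28 df gives 81.3%.
- sVCAM-1: SE = 103 × 0.4472 = 46.06; 148 / 46.06 = 3.21; power 79.6%.

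The stated 80% is reproduced, so it belongs to the trend on assigned dose.

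**2. Scheduled doses from Table 1 (midpoints, 26 weeks).**

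- Low: 45 + 75 + 105 + 135 + 22 × 150 = 3660 min; / 26 = 141 min/wk.
- High: 45 + 75 + 105 + 135 + 165 + 195 + 225 + 255 + 285 + 17 × 300 = 6585 min; / 26 = 253 min/wk.

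**3. Size of the false slope by hand.** Let a share p have an event that multiplies achieved dose by f and adds δ to the biomarker change, with no exercise effect and p equal in all arms. With scheduled dose d and achieved dose D:

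- Cov(D, Y) = -p(1-p)(1-f) × mean(d) × δ
- Var(D) = mean(d²) × (1-p+pf²) - [mean(d) × (1-p+pf)]²

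Take p = 0.20 (the Protocol's dose-modification figure), with f = 0.25 and δ = 30 units (1 SD) assumed, and d = 0, 150, 300. Then mean(d) = 150 and mean(d²) = 37,500.

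- Cov = -0.16 × 0.75 × 150 × 30 = -540.
- Var = 37,500 × 0.8125 - 127.5² = 30,469 - 16,256 = 14,213.
- Slope = -540 / 14,213 = -0.038 per min/wk, or -11.4 units per 300 min/wk.

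Simulation at the same setting gives -11.1, with 5.8% rejections against a nominal 2.5%.

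**4. Simulated range.** No exercise effect, SD 30, 10 per arm, two-sided 0.025, scheduled doses 0/141/253. Assumed: δ = 15-45 units and f = 25-50%. Event shares are 20% (Risk/Benefit Assessment) and 34% (an older-adult exercise trial cited in the Background).

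| Exposure and setting | False positives | Mean slope per 300 min/wk |
|---|---|---|
| Assigned dose, events equal in all arms | 2.3-2.7% | about 0 |
| Achieved dose, 20% events, all arms | 2.6-9.9% | about -4 to -20 |
| Achieved dose, 34% events, all arms | 3.3-20.0% | about -7 to -31 |
| Achieved dose, 20% events, exercise arms only | 1.7-3.1% | about -1 to -10 |
| Achieved dose, 34% events, exercise arms only | 1.3-3.9% | about -1 to -15 |
| Achieved dose, events do not affect biomarker | 2.4-2.6% | about 0 |

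For scale, the planned effect is -44 units at 300 min/wk.

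**5. Exercise arms only.** Here the slope on assigned dose is itself not zero. For doses 0/150/300 it equals p × δ per 300 min/wk, from 0.20 × 15 = +3 to 0.34 × 45 = +15 units. That is a true consequence of assignment under these assumptions, because events then follow from being asked to exercise. Achieved dose reverses its sign.

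**6. Choosing between models.** If an analyst reported whichever of the two slopes was significant, the error rate would be 3.4-4.2% even with no link between events and biomarker (fully assigned doses, ill participants completing 0-50%).

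**The case against.** The case for leaving the text alone has real weight.

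- **Status.** Assigned dose is fitted first, and achieved dose is one of three listed alternatives. A reader might infer that the plan selects it whenever it fits better. The text does not say so: it says fit is assessed and alternatives exist. The defect is an unlabelled permission, not a specified substitution.
- **Event rates.** Neither 20% nor 34% is a control-arm illness rate. The first concerns exercise dose modifications, the second completion of a prescribed dose in another trial. Equal rates in controls are therefore an assumption, and without it most of the excess false positives disappears. The wrong-direction slope in step 5 remains.
- **Illness effect.** No figure in the Protocol supports 15-45 units. Triggers include musculoskeletal and neurologic symptoms, and most training injuries are described as mild. The slope near -31 is the extreme corner: 34% events, 45 units and dose cut to 25%.
- **Recurrences.** Excluding them removes one important way that illness could raise these biomarkers. Other illness stays in.
- **Measurement.** A reader might infer that activity is recorded only in the exercise arms. The Protocol gives every participant a heart-rate monitor and provides accelerometry before and after the study without restriction by arm. What stands is that actual dose is undefined for controls.
- **Secondary outcomes.** The cytokine statement concerns sICAM-1 and sVCAM-1. A reader might extend the direction of bias to insulin or visceral fat, but the Protocol gives no comparable link, and neither was simulated. The loss of the randomised comparison does apply there.
- **Study type.** This is a 39-person feasibility study, which lowers the stakes. It is nevertheless powered for this trend and meant to inform a phase III trial.

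**Conclusion.** The point holds as a fault in how the exposure is defined. Average actual dose is a post-randomisation variable listed as a transformation of dose, with no exploratory label and no meaning fixed for controls. It can bias the primary biomarker slopes towards the hypothesis and forestall the randomised arm comparison.

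The documents do not fix the size. Under the assumed illness effects, false positives run from about the nominal 2.5% to 10% (20% events) or 20% (34% events) if all arms share the event rate. They are about 1-4% if events occur only in the exercise arms, and there is no bias if events leave the biomarker unchanged. The claim that this analysis will produce a false dose-response is not supported; that it could is. It should be fixed, but it does not invalidate the design.

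**What to change.** In both Primary Outcomes and Secondary Outcomes, remove average actual dose from the list of alternatives. State that the linear, log and quadratic forms all use the dose assigned at randomisation, including for participants whose exercise was reduced or stopped. If achieved dose is of interest, report it as a labelled, non-randomised exploratory analysis that cannot replace the primary or secondary test. Confining it to the two exercise arms would also avoid having to define an actual dose for controls.

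The cost is one sentence in each of the two sections. No new data, visits or sample size are needed, and the achieved-dose analysis can still be run. The existing 80% power statement is unaffected, since it already refers to assigned dose.
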